### Plans to promote participant retention and complete follow-up {18b}

At each assessment point (T1 and T2), all patients will receive a phone call from CMs to remind them of the upcoming data collection and free offline consultation with doctors if they attend the assessment. Patients who prematurely discontinue from the study before the 6-month evaluation and do not attend any assessment will have the following evaluations performed, if possible: First, GPs will call them to invite them to insist on the trial or attend the assessment; if refused, a brief interview will be conducted to investigate the reasons for discontinuation. Second, the system log data of these patients will be fully explored to extract useful information.

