### Outcomes {12}

The primary outcome of the trial is changes in mean systolic blood pressure (SBP) from baseline (T0) to 12 months (T2). The key secondary outcomes are changes in mean diastolic blood pressure (DBP) and changes in biochemical indexes related to hypertension from T0 to T2. The other secondary outcomes include changes in lifestyles, self-management adherence, and hypertension awareness from T0 to T1 (6 months) and T2. In addition, work efficiency of care providers will be assessed at T2 to validate the model from a care provider perspective.

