### Methods in analysis to handle protocol non-adherence and any statistical methods to handle missing data {20c}

The statistical analysis will be conducted on an intention-to-treat (ITT) basis. For incomplete assessments (missing data), multiple imputation will be applied using both an optimistic and pessimistic scenario.

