## Discussion

This protocol has been designed to understand the effectiveness of a pathway-driveneHealth-based integrated care model, implemented as a full-featured telehealth system. Compared with prior studies [38, 39], our study innovatively introduces the concept of pathway, then combines it with information technology and the “three-manager” mode to establish a standardized and executable care model. Besides testing efficacy of the model, this study will have several other strengths if successful. First, the model can be generalized to other common chronic diseases, such as diabetes, stroke, and chronic obstructive pulmonary disease (COPD). The task-based pathway can be applied in both single disease and multiple chronic conditions. Second, the study would provide the feasibility evidence of the “three-manager” mode combined with information technology in China. Policy makers in other regions across the country could roll out similar services for better management. Last, the awareness, treatment, and control rates of hypertension in Sichuan, Yunnan, and Guizhou are relatively low compared with other provinces [40]. Therefore, performing such a trial in Yibin is significant to improve the local outcome for hypertension management.

The present protocol is also subject to some limitations. First, since the clients for patients are different from traditional mobile applications, participants may show different levels of acceptance in the system. Low system acceptance will lead to undesirable high attrition rates. We will adopt several strategies to improve patients’ acceptance of the system, including ongoing system updates with usability tests, online system guidance from CMs, and regular offline training sessions for patients. Second, this is an open-label trial for both patients and care providers. Patients in the control group may not comply with self-management regimes or even choose to discontinue the participation, and care providers may tend to conduct the management for the control group not following the guidelines. We plan to eliminate these potential biases through intensive training of care providers and reward mechanism on patients (for example, free outpatient registration), as well as supervision of intervention quality from the steering committee.

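### The recovery procedure for lost patients stops at the 6-month visit, although the primary outcome is measured at 12 months

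*Protocol article*

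**What the plan says.** Section {18b} of the protocol article contains two separate measures.

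- **For everyone:** "At each assessment point (T1 and T2), all patients will receive a phone call from CMs to remind them of the upcoming data collection". Attendance is rewarded with a free consultation.
- **For a subset:** a recovery procedure, to be carried out where feasible, for "Patients who prematurely discontinue from the study before the 6-month evaluation and do not attend any assessment". The first step is that "GPs will call them to invite them to insist on the trial or attend the assessment; if refused, a brief interview will be conducted", to learn the reasons for stopping. The second is that "the system log data of these patients will be fully explored to extract useful information".

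Outcomes {12} defines the primary outcome as "changes in mean systolic blood pressure (SBP) from baseline (T0) to 12 months (T2"). The Blood pressure section states that this change is assessed by clinic measurement; home readings serve daily management. Section {20c} says: "The statistical analysis will be conducted on an intention-to-treat (ITT) basis". Missing assessments are to be multiply imputed under an optimistic and a pessimistic scenario. Sample size {14} requires 171 patients per group at the end of the trial and enrols 402 to allow for 15% attrition. The Discussion, on the open-label design, notes: "Patients in the control group may not comply with self-management regimes or even choose to discontinue the participation".

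**The concern.** The subset is defined by two conditions joined by *and*: leaving before the 6-month evaluation, and attending no assessment. A patient who attends at 6 months (T1) and later stops meets neither. No other section extends the GP call, the interview or the log review to such a patient.

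Because the endpoint is a clinic reading at 12 months (T2), someone who does not attend then has no primary outcome value, whether the loss came in month 3 or month 9. The recovery step therefore covers only the first half of the period in which that value can be lost.

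Two things are at stake: T2 pressures that could have been obtained, and reasons for late dropout that would help to justify the optimistic and pessimistic imputation scenarios. This is more than detail left out of a condensed article, because the article states the rule and sets its limit.

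**Working it through.** **1. Who is covered, reading {18b} as written**

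| Patient | Reminder call and consultation offer | GP call, interview, log review |
|---|---|---|
| Leaves before T1, attends no assessment | Yes | Yes |
| Leaves before T1, still attends T1, misses T2 | Yes | No |
| Attends T1, leaves or misses T2 | Yes | No |

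All three patients lack the T2 clinic systolic pressure.

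**2. The plan's own sample size**

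Inputs from {14}: difference 5 mmHg, SD 16.5 mmHg, α 5%, power 0.80. Section {20a} makes the tests two-sided.

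n per group = 2 × (1.960 + 0.842)² × 16.5² / 5² = 170.9, so 171. This agrees with the protocol.

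Inflation for attrition: 342 / 0.85 = 402.4, against 402 stated. This also agrees to rounding.

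The allowance is 402 − 342 = 60 patients, and it has to cover the full 12 months.

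**3. How many are affected**

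Assumption: losses are even over the year. Then 60 / 2 = 30 patients, 15 per group, are lost after T1. The protocol gives no split by time.

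**4. Effect on power** (two-sample t test, difference 5, SD 16.5, two-sided 5%)

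| Late leavers recovered | Completers per group | Power |
|---|---|---|
| None | 171 | 79.8% |
| Half (171 + 7.5, rounded up) | 179 | 81.6% |
| All (171 + 15) | 186 | 83.0% |

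**5. Illustration of bias**

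Let p_C and p_I be the proportions lost after T1 in the control and intervention groups, and d the difference in mean change between those lost and those who stay, taken as equal in both groups. The completer contrast then departs from the full contrast by (p_C − p_I) × d.

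- 10% against 5%, d = 10 mmHg: 0.05 × 10 = 0.5 mmHg, which is 10% of the 5 mmHg target.
- 15% against 5%, d = 10 mmHg: 0.10 × 10 = 1.0 mmHg, which is 20% of the target.

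All the loss rates and d are assumptions. With 201 per group, the first case means about 20 + 10 = 30 late losses, in line with step 3. The second means about 30 + 10 = 40, so it needs more late loss than step 3 assumes.

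**The case against.** A reader might infer that patients lost after 6 months are not pursued at all. The documents do not support that. The reminder at T2 goes to all patients, carries an incentive, and has no stated exception for those who have stopped using the system. Regular GP follow-up also continues through the year in both groups, and the Discussion adds patient rewards and training sessions. This stands, and it narrows the point. What is missing after T1 is contact after a missed visit or a withdrawal, the interview on reasons, and the log review. The reminder precedes the visit and does not collect reasons.

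A reader might also infer that the protocol expects more loss among controls. It says only that controls may discontinue. The same paragraph names low acceptance of the system as another cause of attrition and ties it to neither group; it could fall more on patients with full access. Unequal loss is a possibility here, and its direction is open.

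The figures invite a further objection, which also stands. The 15% allowance is already in the sample size, so the power gains are gains above plan and depend on an assumed recovery rate. The bias formula describes a complete-case contrast, whereas {20c} plans multiple imputation.

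Finally, use of any T2 reading obtained is arguably implied by the intention-to-treat statement. That is fair, but imputation does not replace a reading that a telephone call might have secured.

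**Conclusion.** The point holds in a limited form. Section {18b} confines its recovery procedure to patients who leave before 6 months and attend no assessment, and so leaves out those lost between 6 and 12 months, although the primary outcome depends on attendance at 12 months. The reading of the text is firm; the size of the consequence is not.

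About 30 patients are affected if the planned attrition is even over the year. Power would rise from 79.8% to at most about 83%. The 0.5 to 1.0 mmHg is illustrative only. The sample size reproduces, and nothing here invalidates the trial or its analysis. This is an inexpensive improvement that reduces avoidable missing primary-outcome data in an open-label trial whose authors recognise that controls may leave.

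**What to change.** Reword {18b} so that the GP contact, the interview on reasons and the log review apply to any participant who discontinues or misses an assessment at any time up to T2, including those who attended T1. State that the contact asks first for the T2 clinic blood pressure measurement, whether or not the patient still uses the system. State that every clinic value obtained this way enters the intention-to-treat analysis. Keep the reminder call and consultation offer as they are.

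The cost is one wording change and about 30 extra calls (half of the 60-patient allowance, if loss is even over the year), made by GPs who already make such calls for early leavers.

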### Data management {19}

In this trial, most of the data during the management process will be recorded by the system and saved in the database. The assessment data will be entered electronically by an investigator. Double data entry will be performed, and all data ranges will be checked again by a different investigator. All patients, physicians, CMs, and GPs have their unique IDs, and their login passwords are encrypted and kept anonymous to the database administrator. The database is also password protected, with access only to the IPs which have been previously registered in a white list. The investigators are only provided with read permission to the database.

### Confidentiality {27}

All records that contain personal information will be stored separately in the database. Only care providers can view the information to conduct the intervention. In data analysis, all data will be treated anonymously. Participants’ personal information will not be released outside of the study without the written permission.

### Plans for collection, laboratory evaluation, and storage of biological specimens for genetic or molecular analysis in this trial/future use {33}

In this trial, a blood collection and a 24-h urine collection will be carried out in HMC for each participating patient at T0, T1, and T2. The blood and urine samples will be used for laboratory tests to assess the biochemical indexes related to hypertension (see Table 2). The test results will be sent to investigators and all samples will not be stored. Investigators will not have access to personal identifiers.

## Statistical methods

### Statistical methods for primary and secondary outcomes {20a}

Statistical analysis will be performed using SPSS version 23.0. All statistical tests will be reported as a two-sided significance level of 5%, and the results will be presented with two-sided 95% confidence intervals (CIs). The data will be treated either by parametric or non-parametric analysis based on the tests for normal distribution (Shapiro-Wilk test) and homoscedasticity (Levene’s test). We will first conduct detailed exploratory descriptive analyses to collected data using graphical and numerical summaries. Then, comparisons between and within groups will be performed to identify the effectiveness. For categorical variables, the Pearson chi-square test or Fisher exact test will be used; for continuous variables, the Student *t* test or Mann-Whitney test will be used. In case of significant baseline differences, a linear mixed model will be constructed for the outcomes adjusting the baseline using the following covariates as appropriate: baseline SBP, demographics (age, gender, education levels), and BMI. Only those confounding factors found to be statistically significant to the outcomes by analysis of covariance will be included in the final model.

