### Eligibility criteria {10}

The inclusion criteria are as follows: (1) 18–80 years old, (2) hypertension diagnosis with uncontrolled blood pressure (BP) for at least 1 year, (3) fluent in Mandarin or Sichuan dialect, (4) able to use the system fluently after instruction, (5) mainly visit the hospital where the trial is hold, and (6) have no walking disability. The exclusion criteria are as follows: (1) participate in another trial within 4 weeks before this study, (2) suffer from mental health problems, (3) suffer from cancer and have received chemotherapy or radiotherapy within half a year before this study, (4) suffer from myocardial infarction, (5) suffer from other serious diseases with natural course shorter than 1 year, (6) have no home internet access, and (7) pregnant or prepare for pregnancy.

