### Sample size {14}

The power calculation is based on the primary outcome measure and aims for a mean systolic blood pressure variation of 5 mmHg with a standard deviation of 16.5 mmHg (the effect size is based on a previous study [29]). Assuming an α of 5%, and power of 0.80, 171 patients per group are required at the end of the trial (342 in total). Considering an attrition percentage of 15%, our aim is to include a minimum of 402 patients at baseline.

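### Pretests decide whether the primary SBP change is compared by means or by ranks, and within-group comparisons are named as evidence of effectiveness; one between-group mean difference should be fixed

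*Protocol article*

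**What the plan says.** The protocol defines the primary outcome under Outcomes {12} as "changes in mean systolic blood pressure (SBP) from baseline (T0) to 12 months (T2"). Sample size {14} "aims for a mean systolic blood pressure variation of 5 mmHg with a standard deviation of 16.5 mmHg", and asks for 171 evaluable patients per group at 80% power.

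The section on statistical methods for primary and secondary outcomes {20a} gives a general rule: "The data will be treated either by parametric or non-parametric analysis based on the tests for normal distribution (Shapiro-Wilk test) and homoscedasticity" (the second test is Levene's). For continuous variables it names Student t or Mann-Whitney. It makes no exception for SBP and promises two-sided 95% confidence intervals for the results. A linear mixed model enters only if baseline differences are significant.

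The same section says that "comparisons between and within groups will be performed to identify the effectiveness". It does not put the between-group contrast first. Intervention description {11a} shows that control patients also receive active, guideline-based follow-up, including adjustment of therapy for those not at target.

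**The concern.** Two stated rules pull the primary analysis away from the question that the trial is sized to answer.

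First, the data choose the estimand. If a pretest rejects, the primary comparison moves from a difference in means to a rank comparison. Mann-Whitney addresses the probability that a patient in one arm has a larger change than a patient in the other. That corresponds to the mean difference only when one arm's distribution is a shifted copy of the other's. After a switch, the promised confidence interval no longer has the target set by the primary outcome and the sample size, and nobody can say in advance which quantity will be reported.

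Second, a before-after change in one arm is treated as a way to establish effectiveness. Both arms are actively managed for a year, so both may fall. A significant fall in the intervention arm, or a significant fall there beside a non-significant one in control, could then be presented as benefit although the arms do not differ.

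**Working it through.** **1. The plan's own figure.** Inputs from Sample size {14}: difference 5 mmHg, SD 16.5 mmHg, power 0.80, alpha 5%. The two-sided level comes from section {20a} and the 1:1 ratio from Trial design {8}.

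n per group = 2 × (1.960 + 0.842)² × 16.5² / 5² = 2 × 7.85 × 272.25 / 25 ≈ 171.

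This reproduces 171 per group, 342 in total. Allowing for 15% attrition, 342 / 0.85 = 402.4, against the stated 402. A one-sided test would need 135 and does not match. The trial is therefore sized on a two-sided, between-group comparison of means. The sample size is not at fault.

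**2. How often the rule switches.** With exactly normal data and three roughly independent pretests at 5% (Shapiro-Wilk in each arm, Levene across arms), the chance that at least one rejects is about 1 − 0.95³ = 0.143. Simulation with 171 per arm, SD 16.5, 3,000 runs per scenario and both arms of the same shape gives:

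| Assumed shape of SBP change | Switch to Mann-Whitney | Type I error, t test | Type I error, two-stage rule | Power at 5 mmHg, t test | Power at 5 mmHg, two-stage rule |
|---|---|---|---|---|---|
| Normal | 0.136 | 0.050 | 0.049 | 0.792 | 0.790 |
| t, 8 df | 0.710 | 0.048 | 0.047 | 0.796 | 0.826 |
| Skewness 0.5 | 0.885 | 0.051 | 0.054 | 0.792 | 0.797 |
| t, 5 df | 0.946 | 0.048 | 0.051 | 0.786 | 0.867 |
| Skewness 1 | 1.000 | 0.057 | 0.048 | 0.804 | 0.859 |

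The simulation error of a 5% rate over 3,000 runs is √(0.05 × 0.95 / 3000) = 0.004, so every type I error in the table is compatible with 5%. Departures that do not invalidate the t test are enough to discard it. Unequal variances alone give no reason either: with SDs differing by a factor of 1.4 and equal arms, the t test's simulated type I error was again 5.0%.

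**3. When the arms differ in shape.** Take equal means and equal SDs, with one arm normal and the other of skewness 1. The pretests then reject in essentially every trial, and the two-stage rule declares a difference in 11.1% of trials, against 5.4% for both the t test and the Welch test. The means are the same; Mann-Whitney is responding to something else.

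**4. Within-group comparisons.** Treat 16.5 mmHg as the SD of change (assumption) and use 171 patients in an arm.

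SE = 16.5 / √171 = 1.26 mmHg.

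For a fall of 4 mmHg the noncentrality is 4 / 1.26 = 3.17, and a two-sided 5% paired test on 170 df is significant with probability 0.883. For falls of 2, 3 and 5 mmHg the probabilities are 0.351, 0.657 and 0.976.

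If both arms truly fall by the same amount, the probability of a significant fall in the intervention arm but not in control is p(1 − p): 0.351 × 0.649 = 0.228 at 2 mmHg and 0.657 × 0.343 = 0.225 at 3 mmHg. The corresponding false between-group result in that direction has probability 0.025.

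**The case against.** Several counter-arguments carry weight.

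- **A reader might infer that pretesting inflates the false-positive rate.** When the arms share a shape it does not: the two-stage error is 0.047 to 0.054, and power is 0.79 to 0.87. The 11% needs arms of different shape, which the protocol gives no reason to expect. Under a pure shift, Mann-Whitney even addresses the same shift as the mean difference. What remains is that the plan cannot know beforehand that this holds, and its primary outcome is a mean.
- **A reader might infer that regression to the mean will produce a fall of predictable size, since entry requires "hypertension diagnosis with uncontrolled blood pressure (BP) for at least 1 year".** The protocol does not support this. Recruitment {15} has eligibility confirmed by telephone, and Implementation {16c} places the baseline clinic measurement after consent. No section screens on that reading or gives a numerical threshold. If selection rests on earlier readings that correlate equally with baseline and 12 months, the expected fall from this source is zero. No size can be attached to it. The within-group point does not need it, because active care in both arms is enough.
- **A reader might infer that a within-arm p-value is the success criterion.** The protocol states no such decision rule and names no paired test. A randomised between-group comparison is also planned, and common falls do not bias it. The fault is narrower: within-group comparisons are given an efficacy role and nothing ranks them below the between-group contrast.
- **The rule is generic and also serves skewed secondary measures, for which rank methods are reasonable.** That is fair, but the section's heading includes the primary outcome and SBP is not exempted.
- **A separate analysis plan may settle the test.** It may, but it would have to override a published rule. This is not a detail left open.

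**Conclusion.** The point holds in limited form. The protocol states a data-driven choice of test that can move the primary analysis away from the mean difference on which the outcome and the 171 per group are built. The switch would happen in about 14% of trials with perfectly normal data, and in most trials under mild assumed skewness or heavier tails. It gains nothing in validity at this sample size. The main damage is to the estimand and its confidence interval; type I error is materially affected only if the arms differ in shape.

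The wording on within-group comparisons is a smaller but real fault: a fall in one arm is not evidence of a treatment effect, whatever its cause, and a 4 mmHg fall would be significant with about 88% probability.

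The switching rates rest on assumed shapes, a 5% level for each pretest, and Shapiro-Wilk applied in each arm. The within-group figures rest on reading 16.5 mmHg as the SD of change. The protocol gives none of these. The conclusion about the estimand depends on none of them.

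**What to change.** For change in SBP from baseline to 12 months, name one between-group analysis of the mean difference with its 95% confidence interval, to be used whatever any pretest shows. A baseline-adjusted linear model or a Welch-type comparison would serve. Keep Mann-Whitney as a sensitivity analysis only. State that effectiveness is judged solely on the between-group difference, and report within-group changes descriptively.

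The cost is analysis wording only. A fixed comparison of mean change keeps 80% power at 171 per group. If 16.5 mmHg is the SD of change, baseline adjustment reduces the residual SD to 16.5 × √((1 + r)/2), where r is the correlation between baseline and 12 months. For assumed r of 0.3, 0.5 and 0.7 this is 13.30, 14.29 and 15.21 mmHg, with power 0.935, 0.899 and 0.860. No further patients or measurements are needed. The change should be made before any outcome data are compared by arm.

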### Trial design {8}

This 1-year study is designed as a randomized, controlled, and non-blinded superiority trial with two parallel groups and repeated measurements at 3 time points (inclusion, at 6 and 12 months). Randomization will be performed as block randomization with a 1:1 allocation. We used the Additional file 1: SPIRIT checklist [24] and the Additional file 2: TIDieR checklist [25] when writing our manuscript.

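### Baseline SBP adjustment depends on a significance test of baseline differences and covariates on their p-values, so the primary model is not fixed and precision is almost always forgone

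*Protocol article*

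**What the plan says.** Statistical methods for primary and secondary outcomes {20a} compares continuous outcomes between groups with a t test or a Mann-Whitney test, the choice depending on Shapiro-Wilk and Levene tests. Adjustment is conditional: "In case of significant baseline differences, a linear mixed model will be constructed for the outcomes adjusting the baseline". The candidate covariates are baseline SBP, age, gender, education and BMI, and they are then screened: "Only those confounding factors found to be statistically significant to the outcomes by analysis of covariance will be included in the final model". The section does not say which baseline variables are tested to decide whether the model is built. No other section names a primary model.

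Outcomes {12} defines the endpoint: "The primary outcome of the trial is changes in mean systolic blood pressure (SBP) from baseline (T0) to 12 months (T2". Sample size {14} "aims for a mean systolic blood pressure variation of 5 mmHg with a standard deviation of 16.5 mmHg" and, with "power of 0.80, 171 patients per group are required at the end of the trial (342 in total", contains no term for baseline adjustment. Trial design {8} states "Randomization will be performed as block randomization with a 1:1 allocation" and describes "repeated measurements at 3 time points (inclusion, at 6 and 12 months".

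**The concern.** When allocation is random, any baseline difference between arms is due to chance, so a test of it answers no useful question. Whether an imbalance matters depends on its size and on how strongly the variable predicts the outcome, not on its p-value. A rule that adjusts only after a significant test has two consequences.

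First, the primary model is unknown until the data are seen. The path runs through tests of normality and variance, then a baseline test, then the covariates' p-values for the outcome. The last step uses outcome data.

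Second, in most trials the rule ends with the unadjusted comparison of change. That comparison does use baseline SBP, because it is subtracted. But subtraction fixes the baseline coefficient at 1, where ANCOVA estimates it. For any correlation below 1 between baseline and 12-month SBP, the change score has the larger variance. The protocol thus gives up precision from a variable that it measures in every participant.

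**Working it through.** **Inputs.** From the protocol: difference 5 mmHg, SD 16.5 mmHg, two-sided 5%, power 0.80, 171 per arm at the end, 402 at baseline (201 per arm). Assumed: the correlation rho between baseline and 12-month SBP, taken over a range because the protocol gives none, and equal SDs at the two visits. The protocol does not say whether 16.5 is the SD of change or of SBP at a visit, so both readings are worked.

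**1. The plan's own figure.** n per arm = 2 × [16.5 × (1.960 + 0.842) / 5]² = 170.95, so 171. Power at 171 is 80.0%. The stated size is that of an unadjusted two-sample comparison.

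**2. Precision.** With visit SD s, the variance of change is 2s²(1 − rho) and the ANCOVA residual variance is s²(1 − rho²). Their ratio is (1 + rho)/2. Power = Φ(5 / [SD × √(2/171)] − 1.960).

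| rho | Variance ratio | 16.5 = SD of change: unadjusted | ANCOVA | n per arm for 80% with ANCOVA | 16.5 = SD at a visit: unadjusted | ANCOVA |
|---|---|---|---|---|---|---|
| 0.3 | 0.65 | 80.0% | 93.5% | 112 | 65.8% | 83.6% |
| 0.5 | 0.75 | 80.0% | 89.9% | 129 | 80.0% | 89.9% |
| 0.7 | 0.85 | 80.0% | 86.0% | 146 | 95.1% | 97.5% |

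At rho 0.8 the ratio is 0.90, and ANCOVA power is 84.0% with 16.5 as the SD of change.

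**3. The rule itself.** It was simulated with 8,000 trials per setting, 171 per arm, 16.5 as the SD of change, and baseline SBP as the only variable tested and the only covariate. About 95% of trials ended with the unadjusted test.

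| rho | Power, protocol's rule | Power, ANCOVA always | Type I error, protocol's rule |
|---|---|---|---|
| 0.3 | 81.2% | 93.2% | 4.1% |
| 0.5 | 80.4% | 89.6% | 4.4% |
| 0.7 | 79.9% | 84.9% | 5.0% |

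The rule captures almost none of the available gain, and it does not inflate the overall type I error. The simulation does not cover the choice between t test and Mann-Whitney or the screening of the other covariates.

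**4. How often the trigger fires by chance.** It fires in 5% of trials if only baseline SBP is tested. If a significant result on any of the five listed covariates counts, and they are independent, it fires in 1 − 0.95⁵ = 22.6%. That is the upper end, since the protocol does not say which variables count.

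**5. A gap just short of significance.** With 16.5 as the SD of change, visit SD = 16.5 / √[2(1 − rho)]. The largest non-significant baseline gap with 201 per arm is 1.96 × visit SD × √(2/201). Left unadjusted, it shifts the change comparison by (1 − rho) × gap.

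| rho | Visit SD | Gap, mmHg | Shift, mmHg | Share of 5 mmHg |
|---|---|---|---|---|
| 0.4 | 15.1 | 2.94 | 1.77 | 35% |
| 0.7 | 21.3 | 4.16 | 1.25 | 25% |

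These shifts are conditional on an uncommon draw: a gap between 1.7 and 1.96 standard errors arises in about 4% of trials. Given a gap of 1.7 standard errors, the unadjusted test's type I error is 11.8%, 10.1% and 8.1% at rho 0.3, 0.5 and 0.7. Given no gap it is 1.5%, 2.4% and 3.4%. Averaged over all draws it is the nominal 5%.

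**The case against.** The best defence is that the rule does little harm overall. Randomisation makes the change-score difference unbiased on average. The overall type I error is 4.1–5.0% in simulation. The sample size was set for the unadjusted comparison and delivers 80% when 16.5 is the SD of change. All of that stands, and it limits the point to precision and pre-specification.

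Three stronger readings are tempting, and the documents do not support them.

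- A reader might infer that baseline SBP is ignored. It is not: the endpoint is a change from baseline.
- A reader might infer that the trial is underpowered. On the SD-of-change reading it is not. Unadjusted power drops below 80% only if 16.5 is the SD at a visit and rho is under 0.5, and the protocol settles neither.
- A reader might infer that the primary comparison is biased or its error rate inflated. That holds only conditional on a near-threshold imbalance, and it is offset by the conservative behaviour when the arms are well balanced.

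It can also be said that a separate analysis plan might settle the model. That would answer a gap, but this is an explicit rule, and an analysis plan would have to overturn it rather than complete it.

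Finally, the gain depends on rho. At 0.8 only 10% of the variance is saved, and on the visit-SD reading at rho 0.7 the gain is 2.4 points of power (95.1% to 97.5%). That is fair, but adjustment loses essentially nothing in a trial of this size.

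**Conclusion.** The point holds as one of lost precision and a primary model left to the data. Over rho 0.3 to 0.7, always adjusting for baseline SBP removes 35% to 15% of the variance of the comparison. It raises power at 171 per arm from 80% to about 93.5–86% with 16.5 as the SD of change, or from 66–95% to 84–97.5% with 16.5 as the SD at a visit. The protocol's rule secures almost none of this. The range of rho, equal visit SDs and the two readings of 16.5 are assumptions. The direction of the result does not depend on them for any rho below 1.

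Overall error control under the baseline trigger is sound. The conditional shift of about 1.2–1.8 mmHg illustrates what an unadjusted near-miss would do and is not an expected bias. This should be fixed, but it does not undermine the design.

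**What to change.** In section {20a}, replace the conditional rule with one primary analysis that applies whatever imbalance is observed: ANCOVA of 12-month SBP (or its change) on arm and baseline SBP, with age, gender, education and BMI as fixed covariates. Report the adjusted mean difference at 12 months with its 95% CI. Delete the baseline significance trigger and the selection of covariates by p-value. Keep the unadjusted t test as a sensitivity analysis. Use the same approach for continuous secondary outcomes, with each outcome's own baseline where it has one.

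A mixed model that also uses 6-month SBP is optional. Trial design {8} implies that measurement, but the outcome and blood pressure sections name only baseline and 12 months for SBP, and ANCOVA at 12 months does not need it.

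The cost is analysis wording only. The covariates are already named, and Implementation {16c} places demographics, body measurement and clinic BP in the baseline assessment. The change should be dated before anyone analyses outcome data by arm; after that the model can no longer be called pre-specified.
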